|                |                                                                                                                                                                                                                                                                                                                                                                                                                                                                                                                                                                                                                                                                                                                                                                                                                                       |
|----------------|---------------------------------------------------------------------------------------------------------------------------------------------------------------------------------------------------------------------------------------------------------------------------------------------------------------------------------------------------------------------------------------------------------------------------------------------------------------------------------------------------------------------------------------------------------------------------------------------------------------------------------------------------------------------------------------------------------------------------------------------------------------------------------------------------------------------------------------|
| Biometry       | 
Efficacy: Comparison of the interventions and control with respect to the HbA1c values after 1 year
 
Description of the primary efficacy analysis and population:
 
The primary endpoint will be analysed using ANCOVA for the HbA1c levels, with the baseline value as covariate and the arm along with stratification variables as factors. Closed testing procedures will be used for the multiple comparisons between arms.
 
Safety: Descriptive statistics will be provided for procedure/device related adverse events by trial arm.
 
Secondary endpoint: Diabetes remission rates will be compared using a chi-squared-test providing an estimate with 95% confidence interval for the relative probability ("risk") of remission rates.
 |

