1. BMI
  - a.  $\geq 27$  to  $< 50$  kg/m^2
  - b.  $\geq 50$  to  $\leq 60$  kg/m^2
2. Current insulin treatment
  - a. yes
  - b. no
3. Sex
  - a. male
  - b. female

The randomization will be performed centrally by the IFB Data Center and will be computer-assisted, using Pocock's minimization algorithm (1). Before start of recruitment, simulations will be performed to demonstrate that the randomisation procedure given the stratification parameters above yields balanced results. A randomisation ratio of 1:1 will be used.

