## 9.4 Sample Size Discussion

On the basis of the important trial by Schauer et al. 2012, the HbA1c-levels can be expected to decrease in the pooled surgery groups by 2.9 (1.7) points and in the conservative group by 1.4 (1.5) points. This already takes into account the expectation of lower initial values for HbA1c in our trial, which, however, has almost no effect on the sample size calculation – only the relative difference between arms matters.

Choosing a 5% significance level, 17 conservative and 119 surgical patients have to be analysed using a t-test to reach 95% power for demonstrating this difference. The analysis with ANCOVA will have higher power still. Expecting a drop-out-rate of 15%, 24 + 68 + 68 patients have to be included, to be analysed: 20 + 60 + 60 (control + stRYGB + clIRYGB).

Even with a pessimistic scenario in which the changes in the surgical group are 1.4 points vs 0.4 points with conservative therapy, the ANCOVA analysis still yields a power of 89%.

With the above sample size and pooling the variance between surgical arms, the width for the confidence interval when comparing the two surgical arms can be expected to be smaller than 1.2 percentage points.

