### 9.5.2 Planned Methods for Analysis

Efficacy: Comparison of the interventions with respect to the HbA1c levels after 1 year

Description of the primary efficacy analysis and population: The primary endpoint will be analysed using ANCOVA for the HbA1c levels, with the baseline value as a covariate and the treatment arm and stratification categories as factors. A closed testing procedure will be used for multiple comparisons. Thus, the three comparisons between the arms will be performed at the nominal significance level of 5% if the global test result is significant. Because the comparison of the surgical groups is of such interest, this comparison will be performed regardless of the result of the global test, though a Bonferroni correction will be used if the global test is not significant.

Secondary endpoint: The comparison of the diabetes remission rates between the surgical arms will make use of a chi-squared-test, and an estimate with 95% confidence interval for the relative probability (“risk”) of remission rates will be provided.

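### Remission is tested without the factors used to minimise allocation, so to the extent that those factors predict remission the test and interval are conservative and lose power

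*Protocol*

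**What the plan says.** Section 9.1 allocates the surgical patients by Pocock minimisation. The factors are BMI class (below 50, or 50 and above), "Current insulin treatment" (yes or no) and sex, and the section adds: "A randomisation ratio of 1:1 will be used".

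Section 9.5.2 carries these factors into the primary HbA1c model, an ANCOVA "with the baseline value as a covariate and the treatment arm and stratification categories as factors".

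For remission, section 9.5.2 says: "The comparison of the diabetes remission rates between the surgical arms will make use of a chi-squared-test". It adds that "an estimate with 95% confidence interval for the relative probability (“risk”) of remission rates will be provided". The Biometry row of the synopsis agrees: "Diabetes remission rates will be compared using a chi-squared-test". No stratum or covariate is named in either place.

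Section 1.1 calls remission at 1 year the key secondary endpoint for the surgical arms, and section 1.2.1 lists this comparison as the second aim.

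**The concern.** Minimisation removes most of the chance imbalance on its factors. The Pearson chi-squared variance is computed as if that imbalance could still occur, because it counts the variation in remission between insulin, BMI and sex groups as noise. If those groups differ in remission, the standard error is too large. The test then rejects too rarely under the null hypothesis, and the interval covers more than 95%.

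A link with insulin use is plausible. Remission requires both HbA1c below 6.5% and no need for antidiabetic drugs (sections 2.2 and 9.2.2). The protocol itself treats the factors as important, since it minimises on them and adjusts the primary analysis for them.

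At stake is the chance of detecting a limb-length difference in remission. Section 9.4 sizes the trial on HbA1c, surgery against conservative care, and gives no power for remission. With 60 per arm and assumed rates of 60% and 80%, a chi-squared test has about 67% power, so there is little to spare.

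**Working it through.** **1. The protocol's own figure.** No rate or power is stated for remission. The nearest figure is in section 9.4: "Choosing a 5% significance level, 17 conservative and 119 surgical patients have to be analysed using a t-test to reach 95% power". The inputs are a difference of 2.9 − 1.4 = 1.5 and SDs of 1.7 and 1.5. The standard error is √(1.5²/17 + 1.7²/119) = √(0.1324 + 0.0243) = 0.396, and 1.5/0.396 = 3.79. An unequal-variance t-test gives 95.2%, so the figure is reproduced. It does not bear on remission.

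**2. Analytic check under exact balance.** Let R² be the share of outcome variance explained by the factors. The true size of a nominal 5% test is 2Φ(−1.96/√(1−R²)), and the interval is too wide by the factor 1/√(1−R²). Assume 45% on insulin, with insulin the only prognostic factor. R² is then 0.45 × 0.55 × (difference in rates)² divided by p(1−p), where p is the overall rate.

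- Remission 35% on insulin, 85% off (odds ratio 0.095): p = 0.625, R² = 0.0619/0.2344 = 0.264, size 2.2%, interval 16.6% too wide.
- 40% and 75% (odds ratio 0.22): p = 0.5925, R² = 0.0303/0.2414 = 0.126, size 3.6%, interval 6.9% too wide.
- 50% and 70% (odds ratio 0.43): p = 0.61, R² = 0.0099/0.2379 = 0.042, size 4.5%, interval 2% too wide.

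**3. Simulated minimisation.** Balance is not exact in practice. The simulation used minimisation on all three factors with an assumed biased coin of 0.8, 136 randomised (68 per arm, section 9.4), 120 analysed after random loss, and 45% on insulin.

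- 35%/85%: chi-squared size 2.7%.
- 40%/75%: chi-squared size 4.3%.
- A Cochran-Mantel-Haenszel test stratified by insulin held 5.1% to 5.4%. With rates rising from 30% to 45% on insulin and 80% to 90% off, or from 25% to 40% and 75% to 90%, it gained 9 to 11 points of power over chi-squared.
- 50%/70%: size 5.1% against 5.4%, power 54% against 55%.

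Under simple 1:1 randomisation the chi-squared test ran at 5.2% in both strong null cases, so the conservatism comes from the minimisation.

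**4. Regression alternatives.** The same design was run with assumed 40% on insulin, 60% remission in the reference arm and a treatment odds ratio of 2.5, 6,000 runs per row. LRT is the likelihood-ratio test from logistic regression on the three factors. Std RR is the standardised adjusted relative risk.

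| Insulin odds ratio | Size %: chi-squared / LRT / std RR | Power %: chi-squared / LRT / std RR | Null coverage of unadjusted RR interval, % |
|---|---|---|---|
| 0.5 | 4.4 / 5.0 / 4.2 | 61.6 / 63.8 / 60.4 | 95.9 |
| 0.33 | 4.3 / 5.6 / 4.5 | 57.1 / 61.3 / 58.0 | 96.1 |
| 0.25 | 4.0 / 5.9 / 4.6 | 55.2 / 60.5 / 57.4 | 96.4 |
| 0.15 | 3.1 / 5.1 / 4.1 | 48.6 / 57.6 / 54.6 | 97.2 |
| 0.1 | 3.0 / 5.6 / 4.6 | 41.2 / 53.9 / 50.7 | 97.4 |

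The LRT runs slightly above 5%, so part of its gain is not real. Against the standardised relative risk, chi-squared is about 1 point better at 0.5 and about 1, 2, 6 and 10 points worse in the rows below.

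**5. Intention-to-treat analysis.** Section 9.5.1 counts missing remission data as no remission. With 8 of 68 lost per arm, unrelated to insulin use (assumed), every rate is multiplied by 60/68 = 0.882. Repeating step 2, size moves from 2.2% to 2.9% (35%/85%) and from 3.6% to 3.9% (40%/75%). Excess interval width falls from 16.6% to 11.4% and from 6.9% to 5.1%.

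**The case against.** The strongest reply is that nothing here is invalid. The unadjusted test does not exceed 5%, the crude relative risk is unbiased, and a simple marginal comparison on a secondary endpoint is a defensible choice. This stands, and it limits the point to efficiency.

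The second reply is that the size is assumed throughout. This also stands. A reader might infer that the type I error must fall well below 5% and that ten or more points of power are lost. The documents do not support that: they give no remission rate, insulin share or prognostic strength. Losses of that order need an odds ratio near 0.1. At 50%/70% the effect almost vanishes, and with non-prognostic factors the chi-squared test is at its nominal level (5.1%).

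Third, the statistical analysis plan may exist and could add an adjusted analysis. That is possible, but the protocol is not silent: it names the test in two places without stratification, while naming the factors for the primary model. A chi-squared test could be read as a stratified one, yet no stratification is stated.

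Finally, stratifying on all three factors gives eight cells for 120 patients. In simulation this had about 3 to 5 points less power than logistic regression. That is a reason to choose the adjusted method with care, not to omit adjustment.

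**Conclusion.** The point holds in conditional form. The protocol fixes an unadjusted analysis of its key secondary endpoint although allocation is minimised on three factors that the primary analysis uses. To the extent that those factors predict remission, the test and interval are conservative.

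With about 60 per arm and 45% on insulin (both complete-case assumptions), chi-squared size is about 2.7% to 4.3% and the power loss about 3 to 11 points for a strong insulin effect (odds ratio about 0.1 to 0.3). The loss is about 0 to 2 points for a moderate effect (about 0.4 to 0.5). The lower figures apply when the comparator is a standardised relative risk, which at odds ratios of 0.25 to 0.33 gains only 1 to 2 points. Losses are somewhat smaller in the intention-to-treat analysis. There is no type I error inflation and no bias. The change is worth making because it is nearly free, not because the planned result would be wrong.

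**What to change.** In section 9.5.2 and the Biometry row of the synopsis, replace the unadjusted test with an analysis that accounts for the minimisation factors. One option is modified Poisson regression with robust variance, or logistic regression, with arm, BMI class, insulin treatment and sex, reporting an adjusted (standardised) relative risk with 95% confidence interval. If logistic regression is chosen, base the test on the standardised relative risk, since the likelihood-ratio test ran at 5.0% to 5.9% at this sample size.

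A simpler alternative is a Cochran-Mantel-Haenszel test stratified by insulin treatment with the Mantel-Haenszel relative risk. It covers only one of the three factors. Do not stratify on all eight combinations. Keep crude remission rates as description.

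The cost is one sentence in two places. The stratification items are already entered at randomisation (section 6.3), so no new data are needed. If the factors turn out to be weakly prognostic, the gain is about nil, and the worst case seen was a loss of about 1 point of power with the standardised relative-risk test.

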## 9.6 Interim Analysis

No interim analysis will be performed.

## 9.7 Final Analysis

Final analysis will be performed when all patients finished the final study visit, all queries were

answered and the study database was closed.

## **10 ETHICAL, LEGAL AND ADMINISTRATIVE ASPECTS**

### **10.1 GCP-Statement**

All persons participating in the conduct of the trial commit themselves to observe the Declaration of Helsinki in the current version, as well as all pertinent national laws and regulations, the ICH guidelines for Good Clinical Practice (GCP) issued in June 1996.

### **10.2 Submission**

The trial can start only after obtaining a positive review by the ethics committee. The written approval of the EC must be filed in the trial master file (TMF). Additionally, every participating centre must receive a copy of these documents to be filed in the investigator site file (ISF).

### **10.3 Protocol Amendments**

Changes made to the protocol that was appraised positively by the ethics committee must be positively reappraised if the changes

- are such that they may affect the subjects' safety, e.g.
- result in further data collection that necessitates changes to the patient information and/or informed consent form,
- affect the interpretation of the scientific documents upon which the trial is based or the significance of the results of the trial,
- significantly affect the leadership or conduct of the trial.

Changes in the trial protocol can only be made by a committee, including the Coordinating investigator, data management and biometry.

## **11 DOCUMENTATION**

### **11.1 Case Report Forms (CRF)**

The clinical CRF will be provided by the [REDACTED] in electronic form. Investigators will connect to the database via internet and input data directly into the eDE database. However, a paper version of the CRF will be available, so data can be documented in case of malfunction of the electronic system. The content of this paper version will then be entered to the database later. Each CRF page should be completed as soon as possible after the respective visit. Each CRF page will be signed electronically. The signatures serve to attest that the information contained in the CRF is true and has not been falsified.

The questionnaires of quality of life, physical activity and the diet protocol will be provided to the patient in paper form and these data will be entered into the eCRF by trial personnel afterwards.

At all times the local principal investigator has final responsibility for the accuracy and authenticity of all clinical and laboratory data entered in the CRF.

As source data are regarded:

- for clinical or demographic data: the patient file
- for resting energy expenditure, MRT and ultrasound data: the print-out
- for questionnaire: the questionnaires / diary filled out by the patients
- laboratory print outs for fasting glucose, fasting insulin, HbA1c and Serum lipids (total cholesterol, HDL-cholesterol, LDL-cholesterol, free fatty acids, triglycerides)

All other scientific data will be transferred directly into the electronic data base.

## 11.2 Data Management

For creation of the study database the EDC Tool eData Entry (eDE) by OmniCom will be used. The database will be validated according to the Standard Operating Procedures (SOPs) of the [REDACTED] prior to data capture.

The information entered into the database by the investigators or an authorised member of the study team is systematically checked for completeness, consistency and plausibility by routines implemented in eDE, running every night. Error messages generated by these routines will be checked by the data management staff. Queries obviously not representing a true problem will be closed. Errors with an obvious solution will be corrected by the KKS staff immediately (self-evident correction).

Discrepancies, errors or omissions will be passed to the investigator or an authorised member of the study team at the investigational site by the query management tool of eDE. The investigator will receive notification of all queries concerning his/her investigational site. The [REDACTED] will supervise and support the solution of the queries. Corrected data will be re-checked by automatic routines during the night after entry. In case a query cannot be solved, the Data Management staff of the [REDACTED] may close the query. This shall happen in agreement with the study biometrician and clarification, if the information addressed by the query is relevant for the results of the study, or not.

During the whole course of the study, a backup of all data is made on a daily basis. Unauthorized access to patient data is prevented by the access concept of the study database which is based on a strict hierarchy and role model. Any change of data (e.g. when data is changed in the database during query management) is recorded automatically via audit trail within the database.

At the end of the study, once the database has been declared complete and accurate, the database will be locked. Thereafter, any changes to the database are possible only by joint written agreement between coordinating investigator, biometrician and data manager.

In 2022 all data will be transferred to the [REDACTED] Conditions as above will be continued.

## 11.3 Archiving

All relevant trial documentation (Trial Master File), the electronically stored data, the original CRFs and the final report will be stored for at least 10 years [REDACTED] completion.

At the investigating sites, the investigators' files, patient identification lists, signed written consent forms, copies of all CRFs and the patients' files will be stored for at least 10 years after the trial's completion.

## 12 SUPERVISION OF THE CLINICAL TRIAL

### 12.1 Access to Source Data

According to ICH-GCP and the applicable German laws, the principal investigator must permit all authorized third parties access to the trial site and the medical records of the trial subjects (source data). These include the clinical trial monitors, auditors and other authorized employees of the sponsor, as well as members of the local or federal authorities. All these persons are sworn to secrecy.

### 12.2 Monitoring

To monitor the study center, on-site monitoring by staff of [REDACTED] is planned.

Following the appropriate analyses according to the principles of risk analysis a risk-adapted monitoring according to class K2 will be performed with respect to the monitoring strategy (frequency/degree of SDV) after.

During the initiation visit at the trial site an introduction to the course of studies, ISF, logistics, SAE management and electronic data entry is done.

Regular monitoring visits are organized according to the quality of the trial site up to three times a year. Scope of these visits is to check compliance of the trial site with the study protocol and GCP rules. For all patients, the informed consent documents will be checked. In addition, source data verification (SDV) of the key data (eligibility criteria, intervention, outcome measures) will be performed routinely in a random sample of 50% of the patients. Details are described in the Monitoring Manual. Monitoring will follow the [REDACTED] SOPs.

At the end of the study, a final visit is carried out.

A Trial Steering Committee consisting of principal and promoting investigator, biometrician, project management and physician will be established, in order to monitor and to supervise the progress of the trial, and to ensure adherence to the protocol. A meeting of the committee will be scheduled every 6 months.

The interventions (stRYGB and cIIRYGB) used in this clinical trial are minimally invasive clinically proven therapies for the treatment of type 2 diabetes. The application of these therapies performed by experienced physicians in clinical practice. Therefore, a Data Monitoring Safety Board is not deemed necessary in this trial.

### 12.3 Independent Supervision of the Trial

We will prepare standard operating procedures for all methodologies involved in treatment and diagnostic methods of this proposed trial. The study will be conducted according to Good Clinical Practice Guidelines ([www.ich.org](http://www.ich.org)) and all study investigators will sign an according statement.

The trial will be performed in cooperation with the IFB Data Centre, which is located at Clinical Trial Centre [REDACTED]

## 13 DATA PROTECTION AND CONFIDENTIALITY

All legal requirements concerning data protection and confidentiality will be respected.

Within this study, personal data from the trial subjects and data regarding the therapy and the course of disease (medical results, types of therapy, medication etc.) will be collected.

The data will be stored and processed in pseudonymized form (i.e. without reference to the patient's name) with the aid of an identification number.

Data will be analysed at the [REDACTED]. The safety concept ensures amongst other things that data access is limited to authorized persons, that measures are taken to prevent loss of data and that the laws pertaining to data protection are observed. The data are protected from third party access and only members of the trial are permitted access. These members are sworn to secrecy.

In the event of withdrawal of consent, the necessity for storing data will be evaluated. Data not needed will be deleted immediately. Personal data will be stored in an anonymous manner after reaching the study aim 10 years at the latest, if there are no other regulatory or contractual time periods for archiving.

#### **Declaration regarding Data Protection**

During data entry, processing and analysis in the [REDACTED] all requirements of the data protection act will be taken into account. Access to the data is strictly limited to authorized persons. Data are protected against unauthorized access.

